**Fig 1 pone.0295845.g001:**
[figure not shown]
Exploratory sequential design.

The aims of this project are:

To design, pilot, and implement a DCE measuring diabetes care preferences in Samoa.To identify and measure the strength of preference and importance of attributes of diabetes care alternatives and standard care options.To identify the trade-offs (i.e., marginal Willingness to Pay (WTP)), participants are willing to make to obtain preferred attributes, and the probability of uptake for such services.To measure longitudinal changes in care preferences over time.

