### Implementation

The finalized DCE instrument will be administered to n = 450 adult Samoans recently diagnosed with diabetes (data collection started August 2023; funded as an aim of 5K01DK132514: The Diabetes Clinical outcomes Associated with Retention and Engagement in Care, in Samoa (Diabetes CARE); PI: [name]). After obtaining written informed consent from all participants, RAs are explaining the study objectives, describing what a DCE is (i.e., an explanation that the presented choice sets represent hypothetical scenarios), and are consistently describing the intended definitions of the included attributes and levels. This latter step is intended to help participants assess levels that may be subjective or unfamiliar. For example, continuous glucose monitoring is an included attribute level. This type of glucose management is not common in Samoa at this time, and further explanation may be needed for some participants [33]. In addition to administering the DCE, RAs are collecting demographic (i.e., sex, age, region of residence), anthropometric (i.e., weight and height, and blood pressure), health, and socioeconomic data (income and assets) from participants. Participants are also being administered diabetes knowledge [77], self-management and distress, and treatment adherence [78] questionnaires. These data will be used to examine whether attribute preferences vary by sex and/or are associated with chronic disease risk, age, socioeconomic position, or levels of diabetes knowledge. Assessments take approximately 30–40 minutes.

Two hundred and twenty participants will be asked to complete additional DCEs at 12- and 24-months post initial assessment. The same DCE instrument will be used to measure how preferences change over time as individuals live and manage their diabetes.

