### Planned statistical analyses

The statistical modeling of the DCE will be based on random utility theory, where participants choose between alternative profiles, and the attribute levels of the favored option is associated with the highest utility (benefit) to the specific participant [79]. A mixed logit model will be used to estimate choice models from the ’first best’ data and to observe the direction of the rank-ordered attribute choices [74, 80]. Rank order logit (ROL) modeling or Exploded Logit Modeling [81–83] will be used to observe a full ranking of the alternatives in all choice-sets (including first-best and second-best options in the same model) [74] and determine the probability that a participant chooses one option over the others, based on the chosen option’s attribute levels, while controlling for random factors and interindividual tastes [26, 71]. These types of analyses are useful for identifying unknown/unobserved heterogeneity of preferences [26, 73, 84] and will allow for analysis of the cross-sectional panel-like data (participants will be completing multiple choice sets and there will be multiple responses per case/participant). Progressive mixed ROL models will be constructed [74]. A mixed logit version of the ROL will be estimated by ’exploding’ the data as outlined in Lancsar et al. (2017) [72]. Briefly, this procedure will allow each choice set to result in five rows of data, with the first three rows (first sub-choice set) indicating the first-best preference (coded as 1, the remaining two alternatives as 0) and the remaining two rows (second sub-choice set) indicating the second-best preference (coded as 1, the remaining alternative as 0) [72]. By organizing the data in this manner, a traditional mixed multinomial logit model can be conducted that assesses the ranked choices [72]. The chosen profiles will be the dependent variable, and the levels of the attributes will be the independent variables (standard care attribute levels will be initially coded as the reference variable). Interaction terms will be introduced in Model 2 to estimate any associations between attributes and sex. Other case-specific characteristics (e.g., age, levels of diabetes knowledge, weight status, etc.) will be interacted with the intercept and selected attributes to explore the effect of participant characteristics on preferences in Model 3. [74]. We plan to use dummy coding (rather than effects level coding) for categorical variables to facilitate ease of interpretation [73, 74, 85]. The models will allow for the identification of which attributes are important (βs with p<0.05; Aim 2), the direction of that importance (positive or negative βs), and the relative importance of attribute levels compared to others (ratio of estimated parameter to relevant comparator; Aim 2). Further, we will be able to illuminate the trade-offs participants are willing to make between attributes, including marginal WTP (Aim 3). Because we will be including cost of treatment as an attribute, we can estimate the marginal WTP for other attributes; generally, marginal WTP can be estimated by dividing the estimated utility coefficient of an attribute by the utility coefficient of the cost of treatment attribute, holding other attributes constant [9, 86]. We will also be able to estimate the probability of participants taking up a care profile with specific attributes [26]. Sensitivity analyses will be undertaken if we suspect that the relative marginal utility of attributes varies due to differences in income levels. This may include exploring whether preference weights, probability of uptake of alternatives, and WTP vary by different income levels (Satisfaction from the attribute may be based on its associated costs; e.g., perceived satisfaction/preferences of care options may differ by participants’ ability to pay compared to their peers) [84, 87]. The distribution (level balance) of the attributes will be checked across the first and second preferred profiles to ensure the DCE is balanced and that logit model properties are met [88, 89].

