
Few longitudinal studies using discrete choice experiments have been undertaken [90], therefore analyses will be largely exploratory. Because time between assessments (12 months) is short, the same DCE instrument will be used at each timepoint [90, 91]. Following best practices, we will analyze models at each timepoint using multinomial logit modeling [91]. The Chow Test Analogue for logistic regression will be used to test whether the models’ attribute coefficients significantly differ between timepoints. The Chow Test Analogue allows for comparative analysis of different regression models fitted to two different data sets [91]. By including demographic, socioeconomic, and care-related questionnaire data into our models, we will be able to explore how external factors, and especially changes in external factors such as income status, care use/disuse, and diabetes management and distress, are associated with changes in preferences over time. In the unlikely case that we experience greater loss to follow-up and attrition than expected, we will use repeated cross-sectional DCE approaches (such as a covariate extended model) to measure if differences in preferences across samples are significant [90]. Analyses will be completed in Stata v. 17 (College Station, TX) using the Choice Models (CM) suite of commands [92].

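### The test of preference change over time (Aim 4) treats repeated answers from the same participants as independent samples and cannot separate changed preferences from changed choice consistency

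*Protocol article*

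**What the plan says.** The fourth aim of the protocol article is "To measure longitudinal changes in care preferences over time". Under Implementation, "The finalized DCE instrument will be administered to n = 450 adult Samoans recently diagnosed with diabetes" and then "Two hundred and twenty participants will be asked to complete additional DCEs at 12- and 24-months post initial assessment". The same section adds: "The same DCE instrument will be used to measure how preferences change over time as individuals live and manage their diabetes".

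The analysis is fixed in the longitudinal paragraph of Planned statistical analyses: "we will analyze models at each timepoint using multinomial logit modeling". Equality of the attribute coefficients between timepoints is to be tested with a Chow test analogue, described as follows: "The Chow Test Analogue allows for comparative analysis of different regression models fitted to two different data sets". Repeated cross-sectional methods are held back for the case of heavier attrition than expected. The paragraph calls the longitudinal work mostly exploratory.

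For the cross-sectional analysis, the same section recognises that "participants will be completing multiple choice sets and there will be multiple responses per case/participant" and uses mixed logit models for that reason. The longitudinal paragraph names no person effect, no clustered variance and no model joining the waves. No scale (error-variance) parameter is mentioned anywhere in the article.

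**The concern.** Two separate features of the planned test need attention.

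**Dependence.** A Chow comparison in likelihood-ratio form assumes that the two fits come from independent data and that choices within each fit are independent. Here each person gives 8 choices per wave, and the same people return. The variance of the difference between the two waves' coefficients then departs from the assumed one in two directions. Clustering within a wave makes it larger. Tastes that carry over between waves make it smaller, because the person-specific part largely cancels. Which effect wins depends on how stable tastes are, and that is the very thing Aim 4 sets out to learn.

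**Scale.** A logit coefficient is preference multiplied by choice consistency. If people answer more (or less) consistently at a later wave, every coefficient is stretched or shrunk by a common factor although preferences are unchanged. The design makes this plausible: the instrument is repeated, and the Implementation section says that some levels, such as continuous glucose monitoring, may be unfamiliar enough at first to need explanation.

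At stake is the reading of Aim 4. A real shift may be missed when tastes are otherwise stable, or a familiarity effect may be reported as a change in what patients want.

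**Working it through.** **The plan's own figure.** Sample size and power gives N ≥ (500 × c)/(T × A). With c = 6, T = 8 and A = 3 this is 3000/24 = 125, which reproduces exactly. It concerns main effects at one wave. No figure is given for Aim 4 or for the 220.

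**Inputs from the article.** 220 followed participants, 9 survey blocks, 8 choice sets, 3 alternatives including the opt-out, 7 attributes, at most 6 levels.

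**Assumptions.** Attributes: linear cost plus six categorical attributes with 6, 3, 3, 3, 3 and 3 levels. The number of coefficients is 1 (opt-out) + 1 (cost) + 5 + 5 × 2 = 17. Coefficient values: opt-out −0.5, cost −0.8, six-level attribute 0.1 to 0.6, three-level attributes 0.2 and 0.5. First-best choices only. Level 0.05 (the article ties p<0.05 to Aim 2 and states none for the Chow test).

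**Tests compared.**
- Planned test, read in its usual form: LR = 2(LL₁ + LL₂ − LL_pooled), referred to chi-square with 17 df.
- Participant-clustered Wald test of β₁ = β₂, with a joint sandwich variance that includes the between-wave covariance.
- The LR test with one free relative-scale parameter (17 − 1 = 16 df).

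**Dependence.** 220 against 220, same block at both waves, no change in mean preferences, 500 runs each (Monte Carlo SE at 5%: √(0.05 × 0.95/500) ≈ 1.0 point):

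| Taste SD | Between-wave correlation | Planned test | Clustered Wald |
|---|---|---|---|
| 0 | n/a | 5.4% | 5.0% |
| 0.5 | 1 | 0.6% | 2.6% |
| 0.5 | 0.5 | 3.8% | 5.4% |
| 0.5 | 0 | 11.8% | 6.2% |
| 1 | 1 | 0.0% | 6.0% |
| 1 | 0.5 | 3.0% | 6.6% |
| 1 | 0 | 16.4% | 4.8% |

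Variants at taste SD 1 (300 runs), planned test at correlation 1 and 0.5: all 450 at baseline against 220 gives 0.3% and 6.7%; a different block at follow-up gives 3.7% and 8.0%.

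A second simulation with other assumptions (19 coefficients, taste SD 0.5, opt-out SD 2, 200–300 runs) gives 0.3%, 4% and 17% for the planned test at correlations 1, 0.5 and 0, and 4–6% for the clustered test. With a true shift in the six-level attribute (0.1 to 0.5) and taste correlation 0.9, power is 24% for the planned test and 50% for the clustered one.

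**Scale.** At wave w, P(j) = exp(λ_w x_j′β)/Σ_k exp(λ_w x_k′β), so what is estimated is λ_w β. The planned null is λ₁β = λ₂β, which fails whenever λ₁ ≠ λ₂ even with β unchanged. Identical preferences, no taste heterogeneity, 200 runs (SE at 5% ≈ 1.5 points):

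| λ₂/λ₁ | Planned test | Clustered Wald | LR with free scale |
|---|---|---|---|
| 1.0 | 7.5% | 7.5% | 7.5% |
| 1.25 | 68% | 67.5% | 6.5% |
| 1.5 | 100% | 100% | 6.0% |

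The second simulation gives 90% for the planned test at a ratio of 1.3.

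**The case against.** The strongest reply is that the article itself calls this analysis mostly exploratory, that no sample size or significance level rests on it, and that it can be redone from the same data. That stands, and it lowers the severity.

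The article also does not state the form of the Chow statistic or its variance estimator, and a fuller plan could specify clustering. That stands for the dependence part, where the figures hold only for the usual likelihood-ratio form. It does not help with scale, because clustering leaves those rejection rates where they were.

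The size of any consistency change is assumed. The article gives no figure for it, and the repeats are 12 months apart. The 68% and 100% therefore show sensitivity, not an expected error rate.

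Four stronger readings should be resisted:
- A reader might infer that Aim 4 has no valid test. With tastes that broadly persist, the dependence problem costs power and does not produce false findings.
- A reader might infer plain type I error inflation. The error runs in both directions.
- A reader might infer that wave-by-wave models cannot show which external factors "are associated with changes in preferences over time". The article says that changes in such factors will enter the models, and a change-by-attribute term in a follow-up model would address this, so the wording is loose but the analysis is not impossible.
- A reader might infer that baseline mixes 450 people with a follow-up of 220. The article does not say which set the baseline model uses, and a condensed article may leave that to the full plan.

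**Conclusion.** The point holds as a should-fix. As written, the test of Aim 4 disregards that the same people answer at each wave, and it compares coefficients that confound preference with choice consistency.

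Under the assumed parameters, and read in likelihood-ratio form, the nominal 5% test rejects about 0–0.6% of the time with stable tastes, about 3–4% at between-wave correlation 0.5 (up to 8.0% in the variants), and about 12–17% when tastes are redrawn. A pure scale change of 1.25 is called a preference change in about 68% of runs, and one of 1.5 in all of them.

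The percentages depend on assumed coefficients, level counts, taste spread and scale ratios. The mechanisms do not: the dependence follows from following the same people, and the scale problem from the logit model itself.

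**What to change.** In the longitudinal paragraph of Planned statistical analyses, replace the Chow comparison with one pooled choice model on the followed participants, using their own baseline plus the 12- and 24-month waves. Include:
- wave-by-attribute interactions;
- participant-clustered standard errors, or the person-level random coefficients already planned for the cross-sectional models;
- a relative-scale parameter for each follow-up wave.

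Test the wave-by-attribute terms jointly after allowing for scale. A full set of interactions and a free scale are not both identified, so each wave comparison loses one degree of freedom (16 rather than 17 in the example above). Alternatively, compare scale-free ratios such as marginal WTP across waves, with participant-clustered intervals. Keep the per-wave multinomial logits as description.

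The cost is revised wording and somewhat more model fitting, with no new data. A heavier model, with random coefficients linked across all waves and three-way covariate terms, is not needed for this repair. One limit: clustering and free scale were each checked separately in the simulations, not in combination, so the combined test should be tried on simulated data before it is fixed in the plan.

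### The Chow comparison planned for Aim 4 treats repeated waves of the same participants as independent data, so its p-value is not valid even as an exploratory result

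*Protocol article*

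**What the plan says.** Aim 4 (Aims and hypotheses) reads: "To measure longitudinal changes in care preferences over time". Under Implementation, "Two hundred and twenty participants will be asked to complete additional DCEs at 12- and 24-months post initial assessment", and "The same DCE instrument will be used to measure how preferences change over time as individuals live and manage their diabetes". The survey has 9 blocks of 8 choice sets (Pilot testing).

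The longitudinal paragraph of Planned statistical analyses fixes both the model and the test. On the model: "we will analyze models at each timepoint using multinomial logit modeling". On the test: "The Chow Test Analogue for logistic regression will be used to test whether" the attribute coefficients differ between waves. It adds: "The Chow Test Analogue allows for comparative analysis of different regression models fitted to two different data sets". It repeats that "the same DCE instrument will be used at each timepoint". It mentions no clustering on participant, no random coefficient and no covariance between waves. It describes the longitudinal analyses as mostly exploratory. A repeated cross-sectional approach is held in reserve for higher attrition than expected.

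The cross-sectional paragraph of the same section takes a different line. It calls the data panel-like because "participants will be completing multiple choice sets and there will be multiple responses per case/participant", and it chooses mixed logit and mixed rank-ordered logit models to allow for preference heterogeneity.

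**The concern.** The usual Chow analogue for logit models compares the pooled log-likelihood with the sum of the separate ones and refers twice the difference to a chi-square. That reference needs independent choices within each wave and independence between the waves. If tastes differ between people, neither holds.

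- **Within a wave.** One person's 8 choices share that person's tastes. A plain multinomial logit ignores this, so its variance is too small and the test tends to over-reject.
- **Between waves.** The same person brings much the same tastes to both waves, so the two sets of estimates are positively correlated. The test ignores this too, so it overstates the variance of the change and tends to under-reject.

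The two errors pull in opposite directions, and nothing in the plan shows which one wins. A real change in preferences could be missed, or a chance difference reported as change. The article's own cross-sectional analysis allows for this dependence, and its longitudinal analysis does not.

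**Working it through.** **The plan's own figure.** Sample size and power gives N ≥ 500c/(T × A). With c = 6, T = 8 and A = 3, this is 500 × 6 / (8 × 3) = 3000/24 = 125, as stated. It is a cross-sectional rule. The article states no power or error rate for the Aim 4 comparison, so that was simulated.

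**Inputs from the article.** 220 followed participants (450 at baseline), 8 choice sets, 9 blocks, 3 alternatives including the opt-out, 7 attributes with 3 to 6 levels, cost continuous. One wave of the followed group gives 220 × 8 = 1,760 choices from only 220 people.

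**Assumptions (not in the article).**
- First-best choices only.
- Six categorical attributes with 3, 3, 3, 4, 4 and 6 levels. Coefficients: 1 (cost) + 2+2+2+3+3+5 (levels) + 1 (opt-out) = 19.
- Normal person-level tastes with standard deviation SD, correlated ρ between waves.
- Level 0.05 for the Chow test. The article states p<0.05 for Aim 2 only.

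**Tests compared, for two waves.**
- Chow analogue: LR = 2(LL₁ + LL₂ − LL_pooled), against chi-square with 19 df.
- Person-clustered: W = d′V⁻¹d, where d is the vector of coefficient changes and V sums each person's contribution over both waves. W(n−K)/(K(n−1)) is referred to F(K, n−K), with K = 19; for n = 220 that is F(19, 201).

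The first test in effect uses Var(b₁) + Var(b₂) with model-based variances. The correct variance of b₂ − b₁ uses person-clustered variances and subtracts the covariances between waves.

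**Rejection rate with no true change (nominal 5%), Chow analogue, 220 v 220.**

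| Taste SD | Block at follow-up | ρ = 0 | ρ = 0.5 | ρ = 0.8 | ρ = 1 |
|---|---|---|---|---|---|
| 0.5 | same | 8.5% | 2.8% | 1.5% | 0.8% |
| 1.0 | same | 16.5% | 2.5% | 0.5% | 0% |
| 0.5 | different | 8.5% | 7.0% | 5.0% | 4.0% |
| 1.0 | different | 17.5% | 9.3% | 5.8% | 3.0% |

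With no heterogeneity (SD 0, same block) the rate is 4.8%, so the simulated test is correct when its assumptions hold. If all 450 baseline participants are compared with the 220, at SD 1.0 and same block, the rates are 12.5%, 5.0%, 2.5% and 0% across the four values of ρ.

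The clustered test rejected 3.5-7.5% with 220 per wave and 4.5-8.5% with 450 v 220.

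**Power, 220 v 220, same block.** The shift is in one attribute level and in cost.

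| Taste SD | ρ | Shift (level / cost) | Chow | Clustered |
|---|---|---|---|---|
| 0 | – | 0.4 / 0.2 | 89.5% | 85.5% |
| 0.5 | 1 | 0.4 / 0.2 | 56% | 76.5% |
| 1.0 | 0.8 | 0.4 / 0.2 | 13.5% | 41% |
| 1.0 | 1 | 0.4 / 0.2 | 6% | 58.5% |
| 1.0 | 1 | 0.6 / 0.3 | 53.5% | 98.5% |
| 1.5 | 1 | 0.6 / 0.3 | 2% | 87.5% |

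**Precision.** Cells used 400 replicates, or 200 for power, for 450 v 220, and for SD 1 with ρ = 1. At a true 5%, the Monte Carlo standard error is √(0.05 × 0.95/400) = 1.1 points, or √(0.05 × 0.95/200) = 1.5 points.

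**The case against.** The article never uses the word independent and does not write out the test statistic. A cluster-robust Wald version would cure the problem, and a condensed article often leaves the variance estimator to a fuller plan. Multinomial logit might also be shorthand for the mixed model of the preceding paragraph. Neither reading has support in the longitudinal paragraph, which names a plain model and a test described as working on two different data sets. A mixed logit fitted separately to each wave would still ignore the pairing between waves. What stands is that the fault is shown for the test in its usual form.

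The exploratory label also stands. The article sets no error level or decision rule for Aim 4, so no confirmatory claim is at risk.

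Some stronger inferences are not supported:
- *That the test will lose most of its power.* That happens here only at taste SD 1 or more with tastes that are highly stable. At SD 0.5 the loss is moderate, and the article gives neither SD nor ρ.
- *That over-rejection is as likely as conservatism.* With the same block repeated, over-rejection appeared only at ρ = 0. The same instrument is planned, though the article does not say whether each person keeps the same block.
- *That a two-sample test cannot serve three waves, that it cannot measure change, or that multiplicity is a fault.* Pairwise comparison is a natural reading, the coefficients are estimated at every wave, and control of multiple testing is optional in exploratory work.

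**Conclusion.** The concern holds. The method named for Aim 4, as ordinarily run, does not suit repeated responses from the same 220 people, and its p-value cannot be taken at face value. This is an unsuitable stated method, not an omitted detail.

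The conclusion that the reference distribution is wrong needs only that tastes differ between people, which the article expects. The size of the error rests on the assumed taste SD, the between-wave correlation and whether blocks repeat. The most plausible direction under the plan, with the same instrument and reasonably stable tastes, is a conservative test that misses real change, provided each person also keeps the same block. Because the analysis is exploratory, the change should be made but does not put the study's main results in doubt.

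**What to change.** In the longitudinal paragraph of Planned statistical analyses, replace the Chow comparison with one stacked choice model over all waves of the followed participants. Include wave-by-attribute-level interactions and cluster the variance on participant across waves. A panel mixed logit with person coefficients shared or correlated across waves is an alternative, and is closer to the cross-sectional analysis. Test change with a joint Wald/F test and report each change with its 95% CI. State also whether each participant receives the same block at every wave.

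The cost is a change of wording and a few lines of code. No new data are needed. The small downside is that a robust Wald test with many interactions and 220 clusters can be slightly off nominal (3.5-7.5% in the simulation), so an F reference should be used.
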